## **2 SCIENTIFIC RESEARCH JUSTIFICATION**

### **2.1 Current state of knowledge with regard to research**

#### **2.1.1 On the pathology**

The current COVID-19 epidemic is responsible for a significant number of severe hypoxemic respiratory distress that initially requires oxygen therapy (up to 15 L/min). This respiratory distress progresses to adult respiratory distress syndrome (ARDS) with the need for mechanical ventilation in intensive care. During ARDS, mechanical ventilation is based on the application of small tidal volumes (6 ml/kg), titrated end-tidal pressure to achieve the best pulmonary compliance without exceeding a plateau pressure of 30 cm H2O and daily prone positioning (PP) when the P/F ratio < 150. Prone positioning showed a survival benefit in non-COVID ARDS, linked to a better distribution of pulmonary ventilation. However, despite this optimized management of ARDS including PP, Chinese intensive care colleagues report a mortality of around 50% of COVID ARDS treated in intensive care. Before admission to the ICU, patients with COVID pneumonia go through different stages of oxygen requirements, but we observed that an oxygen requirement of 3L/min in the acute phase of the disease is strongly associated with the occurrence of severe respiratory distress.

#### **2.1.2 On the reference strategies/procedures**

The management of respiratory distress related to COVID-19 infection has just been the subject of two recommendations issued by the "surviving sepsis campaign" and by the World Health Organization.

In patients breathing spontaneously, it is recommended to administer oxygen therapy to achieve a SpO2 between 92 and 96%. If standard oxygen therapy is insufficient, it is recommended to use high-flow nasal oxygen therapy up to 60L/min rather than non-invasive ventilation. If the latter is insufficient, then intubation for mechanical ventilation is necessary. Administration of a tidal volume between 4 and 8 mL/kg and the use of a positive end expiratory pressure (8 to 14 cmH2O) without exceeding a plateau pressure of 30 cmH2O are recommended. Prone position is used when the PaO2/FiO2 ratio is less than 150 in mechanically ventilated patients.

There is no recommendation on the positioning of patients on spontaneous ventilation. Usually, in the ward or in intensive care, patients on oxygen therapy for pneumonia remain in the supine position. Daily prone positioning could improve pulmonary ventilation in patients on spontaneous ventilation and thus prevent intubation.

### **2.2 Research hypothesis**

We hypothesize that the prone position of patients in spontaneous ventilation (=not intubated) from the oxygen requirement stage of 3L/min prevents respiratory deterioration in COVID-19 patients. This early stage PP is easy to perform because patients can mobilize themselves to make the change of position. In addition, prevention of some of the severe respiratory distress is a major objective during an epidemic during which resources in intensive care beds are limited.

### **2.3 Description of the population to be studied and justification for its choice**

Adult COVID-19 patients (PCR or typical CT imaging), not intubated, requiring oxygen therapy at a rate of at least 3L/min to get a peripheral saturation greater than or equal to 95%.

We observed during the recent management of patients in the context of the current COVID epidemic that oxygen supply at more than 3L/min was associated with a high proportion of deterioration with severe respiratory distress.

Thus, among patients admitted to hospital in China for COVID-19 pneumonia, 26% are secondarily admitted to intensive care, among which 50% of patients require mechanical ventilation. However, only 80% of patients were oxygen-requiring in the Guan et al. series. Including patients requiring at least 3L/min of oxygen, some of which will be included in the intensive care unit and already on high-flow oxygen therapy, we estimate that 20% of the patients included will require mechanical ventilation or die in the arm without prone positioning.

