| Practical procedure                             | Patients who meet the criteria and are admitted to the COVID ward will be offered to participate in the study orally and then a written consent will be obtained. Notification of the patient's participation in this study will be listed in the patient's medical record.

Randomization will be done via cleanweb. A paper CRF will be completed in each centre and sent by photo or scan to the CRU for collection in the e-CRF. Following randomization, patients in the interventional group will be instructed to spend at least 6 hours on their stomach (PP). They will get into the position on their own and regularly note the time spent in PP. Patients in the control group will do as usual without external intervention on the positioning to be adopted. It will thus be possible to compare the expected results of the group in PP at least 6 h/24h to the group with standard behavior. |
| Number of Selected Subjects                     | At least 500 patients                                                                                                                                                                                                                                                                                                                                                                                                                                                                                                                                                                                                                                                                                                                                                                                                                                                                                               |

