| Statistical analysis                              | 
This is a Bayesian study whose analysis will be based on the calculations of the a posteriori probabilities for a number of hypotheses. There is therefore no fixed sample size as in a frequentist analysis. The stopping rules will be based on the probability calculations conditional on the data of an <math>OR > 1</math>, corresponding to a non-zero effect, but also of an <math>OR > 1.05</math> corresponding to a more marked effect, but also on the probabilities of <math>OR < 1</math> ineffectiveness or of a marked deleterious effect <math>OR < 0.95</math> with respective probability thresholds set at 0.95, 0.80, 0.8, 0.75. Vague priors but adapted to Bayesian studies using ORs will be used. The maximum size of the study is set at <math>N=500</math> patients (based on the size of a frequentist study with a power of 80% to demonstrate a difference of 10% between the 2 groups (i.e. 25% vs 15%). The simulations carried out show a high probability that the study will be conclusive after the inclusion of less than 300 patients.
 |
| Source of funding                                 | Submission to the PHRC (Ministry of Health and Solidarity) COVID                                                                                                                                                                                                                                                                                                                                                                                                                                                                                                                                                                                                                                                                                                                                                                                                                                                                                                                                                                                                                         |

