## 4 RESEARCH DESIGN

### 4.1 Primary endpoint

**Composite Outcome** : Achievement of one of the following criteria (if absent at the time of randomization):

- Use of intubation
- Death

Criteria assessed up to 28 days after inclusion

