## 5 DESCRIPTION OF THE RESEARCH METHODOLOGY

### 5.1 Experimental design

Comparison of two positioning strategies to prevent respiratory complications related to COVID-19 respiratory infections

Randomized study, two comparison groups

**Group A:** interventional group: Patients will be instructed to spend at least 6 hours in the prone position (PP). They will put themselves in the position and regularly note (or the nurse in charge) the time spent in PP on a specific document provided by the research. Patients will lie on their stomach with their head turned to the side and a cushion placed under the chest at their convenience.

**Group B:** control group: Patients will not have any particular positioning instructions.

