## 13 STATISTICAL ASPECTS

### 13.1 Description of the planned statistical methods:

#### **Study size:**

This is a Bayesian study whose analysis will be based on the calculations of the a posteriori probabilities for a number of hypotheses. There is therefore no fixed sample size as in a frequentist analysis. The stop rules will be based on the probability calculations conditional on the data of an  $OR > 1$ , corresponding to a non-zero effect but also of an  $OR > 1.05$  corresponding to a more marked effect, but also on the probabilities of  $OR < 1$  ineffectiveness or of a marked deleterious effect  $OR < 0.95$  with respective probability thresholds set at 0.95, 0.80, 0.8, 0.75. Vague priors but adapted to Bayesian studies using ORs will be used. The maximum size of the study is set at  $N=500$  patients (based on the size of a frequentist study with a power of 80% to demonstrate a difference of 10%

between the 2 groups (i.e. 25% vs 15%). The simulations carried out show a high probability that the study will be conclusive after the inclusion of less than 300 patients.

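### The 500-patient cap is justified with a 25% control event rate while section 2.3 expects 20%, and 500 is called both a maximum and a minimum

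*Protocol*

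**What the plan says.** **Control rate.** Section 2.3 starts from published series: 26% of admitted patients go to intensive care, half of those are ventilated, and only 80% of one series needed oxygen. Allowing for the sicker patients this trial will include, it concludes: "we estimate that 20% of the patients included will require mechanical ventilation or die in the arm without prone positioning". That is the composite of section 4.1 (intubation or death, "Criteria assessed up to 28 days after inclusion") in the control arm.

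**Size.** Section 13.1 (Study size) calls the trial Bayesian and says "There is therefore no fixed sample size as in a frequentist analysis". It then sets the cap: "The maximum size of the study is set at" 500. The basis is a frequentist study, described in the synopsis row on statistical analysis as one "with a power of 80% to demonstrate a difference of 10% between the 2 groups (i.e. 25% vs 15"%).

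**Floor or cap.** The synopsis row on the number of subjects reads "At least 500 patients". The synopsis statistical row and section 13.1 both make 500 the maximum. The table in section 7.3 lists 500 as the total.

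**The concern.** Two statements about the same quantity disagree. The only control rate with a derivation is 20%. The rate that carries the sample size is 25%, and it has none. Nothing links the two, so a reader cannot tell what the authors believe 500 patients can show.

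Separately, 500 cannot be both a floor and a cap. In a design with looks every 50 patients, the maximum size is one of the quantities that fix the operating characteristics, along with the thresholds, the look schedule and the priors. The plan should therefore state it one way.

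Size, cap and expected event rate are what an ethics committee and later readers use to judge whether the trial was worth running.

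**Working it through.** **Inputs.** From the protocol: control rate 20% (section 2.3); 25% versus 15%, 80% power and 500 patients (section 13.1 and synopsis). Not stated in the protocol and assumed here: two-sided 5% test, 1:1 allocation (section 5.1 says only "Randomized study, two comparison groups") and no dropout inflation.

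**Formulas.** Pooled-variance comparison of two proportions, with p̄ = (p1 + p2)/2:

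- n per arm = [1.96·√(2p̄(1−p̄)) + 0.8416·√(p1(1−p1) + p2(1−p2))]² / (p1−p2)²
- power = Φ{ [ |p1−p2| − 1.96·√(2p̄(1−p̄)/n) ] / √[(p1(1−p1) + p2(1−p2))/n] }

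**Step 1: the protocol's own figure.** p1 = 0.25, p2 = 0.15, p̄ = 0.20.

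- n = (1.96·√0.32 + 0.8416·√0.315)² / 0.01 = (1.1087 + 0.4724)² / 0.01 = 249.98, so 250 per arm and 500 in total.
- Power at 250 per arm is 80.0%.
- Other conventions give 496 (unpooled), 540 (continuity-corrected) or 394 (one-sided 5%). The exact match supports the two assumptions on the test and the allocation.

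**Step 2: the effect implied by 25% versus 15%.**

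- Relative risk 0.15/0.25 = 0.60
- Odds ratio (0.15/0.85)/(0.25/0.75) = 0.529, or 1.89 if expressed so that a value above 1 means benefit
- Absolute difference 10 points

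**Step 3: carry each effect to a 20% control rate, 250 per arm.**

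| Effect kept | Rates | Power | Total N for 80% |
|---|---|---|---|
| Relative risk 0.60 | 20% vs 12% | 68.5% | 658 |
| Odds ratio 0.529 | 20% vs 11.7% | 72.2% | 604 |
| 10-point difference | 20% vs 10% | 88.2% | 398 |

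The 11.7% comes from odds of 0.25 × 0.529 = 0.1324, and 0.1324/1.1324 = 0.117. As an example of the power calculation, for 20% vs 12% it is Φ[(0.080 − 0.0643)/0.0326] = Φ(0.48) = 68.5%.

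**Step 4: where 80% is reached.** At a 20% control rate and 250 per arm, 80% power is reached at about 20% vs 10.96%, roughly 11%. That is a 45% relative reduction (odds ratio 2.03), against the 40% reduction (odds ratio 1.89) in 25% vs 15%.

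**Step 5: the rule the trial will use.** I simulated the stopping rules of section 13 with these assumptions: near-flat prior with a normal approximation, OR above 1 read as benefit, binding stops from the second look (100 patients), and a maximum of 500.

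- Efficacy is declared in about 96% of trials at 25% vs 15%, 94% at 20% vs 11.7%, and 93% at 20% vs 12%.
- With 20% in both arms it is declared in about 35 to 36%.
- Letting recruitment and looks run past 500 moves that no-effect figure from about 35% to about 37% at 600, 38% at 800 and 39% at 1000.

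**The case against.** **The 80% is only a benchmark.** Section 13.1 disclaims a fixed sample size and uses the frequentist calculation to place the cap. This stands. The 80% should not be read as a claim about the Bayesian design, and the 69%, 72% and 88% above must not be presented as one either.

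**The protocol states its effect as an absolute difference.** Keeping 10 points at a 20% control rate raises the benchmark power to 88%. This also stands. A reader might infer that power simply falls to 69–72%, but the document does not support that without a condition on scale. The odds ratio is a natural scale because every posterior threshold in section 13 is an odds ratio, but choosing it is the reader's step. Keeping 10 points is also a choice: it enlarges the assumed effect from a relative risk of 0.60 to 0.50. A reader might also infer that only a halving of risk keeps power at 80%. Step 4 shows that about 20% vs 11% is enough.

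**The 20% might be the average over both arms.** The mean of 25% and 15% is indeed 20%. But section 2.3 assigns its 20% explicitly to the arm without prone positioning, so the text does not allow that reconciliation.

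**The floor wording is one synopsis cell.** The statistical text twice says maximum and section 7.3 lists 500. That makes the cap the likelier intent. A reader might infer that recruitment will run on past 500 and badly inflate false positives. The documents do not say so, and under the assumptions of step 5 the increase is only a few points.

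**Conclusion.** The point holds as two unreconciled inconsistencies. The control-arm rate is 20% where it is derived and 25% where it is used, with no source for 25%. And 500 is a minimum in one synopsis row but the maximum in another and in section 13.1.

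The arithmetic behind 500 is correct for the rates it uses. At the protocol's own 20%, the fixed-sample benchmark for 500 patients lies between about 69% and 88%, depending on whether the relative risk, the odds ratio or the absolute difference is held. This range rests on a two-sided 5% test and 1:1 allocation, which the protocol does not state but which reproduce 500.

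A reader might conclude that the trial is underpowered. The documents do not support that, because the benchmark test is not the planned analysis. Under the assumptions of step 5 the planned rule declares efficacy in about 94% of trials at 20% vs 11.7%. It also does so in about 35 to 36% with no effect, so the 80% describes neither the power nor the error of the design.

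**What to change.** 1. Use one control rate in section 2.3, section 13.1 and the synopsis: 20%, or 25% with its justification added to 2.3.
2. Name the scale on which the target effect is defined, with the test, sidedness and allocation behind the calculation.
3. Restate on that scale the fixed-sample power that 500 patients give, and label it as a benchmark for the cap and not as the power of the Bayesian design.
4. Report separately, at the chosen control rate, the simulated probability of declaring efficacy under the section 13 stopping rules, for the target effect and for no effect, with the priors used.
5. Change the synopsis row on the number of subjects to at most 500 patients.

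The cost is wording and a simulation, possibly a less favourable stated figure. No extra patients are needed, and the endpoint does not change.

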## **2.4 Description of the acts performed or products used in accordance with their current use**

Patients receive oxygen therapy through a mask, or even high-flow nasal oxygen therapy or non invasive ventilation to achieve an SpO2 between 96% and above. Patients are usually placed in the supine position with the torso raised at 30°. An arterial catheter (radial or femoral) is placed in response to the need to take regular check-ups (blood gases in particular) to monitor the respiratory function of patients. A central venous catheter is placed when the patient requires sedation and/or catecholamine administration to maintain an average blood pressure level above 65 mmHg. In the case of intubation, the patient is intubated by the orotracheal route and is connected to a ventilator for the delivery of a tidal volume of 4 to 8 mL/kg, a PEEP of 8 to 14 mmHg without exceeding a plateau pressure of 30 cm of H2O.

## **2.5 Description of acts and procedures added by the research**

Prone position for at least 6 hours / 24 hours is added as well as the fact that the patient (or the nurse in charge) has to note alone the time spent in the position on a specific document provided by the research. Patients will lie on their stomach with their head turned to the side and a cushion placed under the chest at their convenience.

We do not want to overload caregivers, which is why we will only recruit patients who are completely autonomous. Caregivers will remind patients to remember to move to the prone position and note the time spent in this position only at times of care. No reminders outside of the field, so no additional contacts induced by the research.

## **2.6 Summary of foreseeable and known benefits and risks for research participants**

By avoiding intubation of patients with COVID-19 hypoxemic respiratory failure thanks to prone positioning, we believe we can improve lung aeration, improve patient oxygenation, prevent intubation, and improve survival. The second expected benefit is the optimization of the management of ICU beds on a just-in-time basis during this pandemic period.

In some people, the prone position can induce discomfort, which, if not tolerated, can be divided at the discretion of the patient.

# **3 RESEARCH OBJECTIVES**

## **3.1 Main objective of the research**

To show that daily prone positioning (objective of at least 6 hours/day) in COVID-19 patients with respiratory failure requiring oxygen therapy of at least 3L/min to obtain a saturation  $\geq 95\%$  reduces the proportion of patients requiring intubation and/or death.

### 3.2 Secondary Research Objectives

To show that daily prone placement (objective of at least 6 hours) in COVID patients with respiratory involvement requiring oxygen therapy of at least 3L/min decreases:

- the proportion of patients admitted to intensive care (among those who were in the conventional hospitalization department at baseline)
- the use of intubation
- the use of non-invasive ventilation or high-flow oxygen therapy (for those who were not already receiving it at baseline)
- length of ICU stay
- length of hospital stay
- the maximum flow rate of oxygen therapy (nasal or mask)

## 4 RESEARCH DESIGN

### 4.1 Primary endpoint

**Composite Outcome** : Achievement of one of the following criteria (if absent at the time of randomization):

- Use of intubation
- Death

Criteria assessed up to 28 days after inclusion

### 4.2 Secondary endpoints

- The proportion of patients admitted to intensive care (among those who were in the conventional hospitalization department at baseline)
- Number of days alive without invasive ventilation in the first 28 days
- Number of days alive out of intensive care in the first 28 days
- Number of days alive out of hospital in the first 28 days
- Number of days alive without NIV or high-flow oxygen therapy in the first 28 days (for those who did not benefit at baseline)
- Maximum Flow Rate of Oxygen Therapy Over 28 Days

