### - Recruiting Centres

Conventional hospitalization services dedicated to the care of COVID-19 patients will receive patients who meet the inclusion criteria (non-intubated patients requiring 3L/min of O2 or more to obtain a peripheral saturation greater than 95%). The intensive care units will also include patients (either on simple oxygen therapy, on high-flow oxygen therapy, or on non-invasive ventilation) on these same criteria.

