### 6.1.2 Follow-up visits

From this point on, patients in the interventional group (Group A) will be instructed to spend at least 6 hours on their stomach (PP). They will put themselves in the position. They will stand on their stomach with their head turned to the side and a cushion placed under the chest at their convenience and will regularly note the time spent in PP. They (or the nurse in charge) will have at their disposal a collection sheet and a pen.

Patients in the control group (Group B) will do as usual without external intervention on the positioning to be adopted.

For a maximum of 28 days, a daily reading of the

- Vital status
- Transfer to intensive care for patients included in a ward unit

- Use of intubation
- Use of an alternative ventilation technique (NIV, high-flow nasal oxygen therapy)
- Maximum Oxygen Therapy Flow Rate (Nasal or Mask)

At the end of the stay (maximum on the 28th day): we will collect

- Length of ICU stay
- Length of hospital stay

If the patient is discharged before day 28 (maximum duration of study participation)

- Your vital status will be searched for up to 2 months after discharge by phone call

The total duration of the study will be 19 months.

|                                       |                                                              |
|---------------------------------------|--------------------------------------------------------------|
| Length of Inclusion Period            | 18 months                                                    |
| Duration of participation of subjects | 28 days                                                      |
| Search for vital status               | Up to two months after discharge from hospital by phone call |

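### Days alive without NIV or high-flow oxygen counts days on invasive ventilation as success days, so it can rank an intubated survivor above a patient who recovered on high-flow

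*Protocol*

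**What the plan says.** The endpoint in Protocol section 4.2 is "Number of days alive without NIV or high-flow oxygen therapy in the first 28 days (for those who did not benefit at baseline". The synopsis (section 1) and the secondary endpoints under section 9.1 use the same definition. The only restriction concerns support at baseline; none of the three places says how to score a day on an invasive ventilator.

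The objective behind it, in section 3.2, is to reduce "the use of non-invasive ventilation or high-flow oxygen therapy (for those who were not already receiving it at baseline".

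The Protocol treats invasive ventilation as a separate item. Section 4.2 has its own 28-day count of days alive and free of it. Section 6.1.2 records intubation daily on one line and "Use of an alternative ventilation technique (NIV, high-flow nasal oxygen therapy" on another.

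Section 2.1.2 sets out the order of escalation. When standard oxygen is not enough, "it is recommended to use high-flow nasal oxygen therapy up to 60L/min rather than non-invasive ventilation"; when that fails, the next step is intubation.

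**The concern.** A day scores as a success if the patient is alive and on neither NIV nor high-flow. A ventilated day of a living patient meets both conditions. Moving from high-flow to a ventilator, which is a deterioration on the Protocol's own ladder, therefore stops the loss of days.

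The wording already makes death a failure state, so dying is not credited as freedom from support. The same reasoning applies to intubation, but the definition does not carry it through.

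What is at stake is the reading of one secondary result. Section 13.1 gives each secondary criterion its own posterior probabilities and 95% credibility interval. A treatment that prevents intubation could show fewer days alive without NIV or high-flow, and a treatment that increases intubation could show more.

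**Working it through.** **The plan's own figure.** No target or effect size is stated for this endpoint. The only reproducible design figure is the maximum of 500, which belongs to the primary endpoint. For 25% vs 15% at 80% power, assuming two-sided alpha 0.05, 1:1 allocation and no continuity correction:

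n per arm = [1.96·√(2·0.20·0.80) + 0.8416·√(0.25·0.75 + 0.15·0.85)]² / 0.10² = (1.1087 + 0.4724)² / 0.01 ≈ 250, so 500 in total.

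It reproduces, and nothing below changes it.

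**Step 1: single histories.** Let H be days on NIV or high-flow, V days on invasive ventilation and D days dead, within 28.

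- As written: 28 − D − H
- With invasive ventilation as a failure state: 28 − D − H − V
- Existing ventilation-free-days endpoint: 28 − D − V

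| Illustrative history | As written | Ventilated days also fail | Ventilation-free days |
|---|---|---|---|
| No NIV, high-flow or ventilator | 28 | 28 | 28 |
| High-flow 7 days, recovers | 28 − 7 = 21 | 21 | 28 |
| High-flow 2 days, ventilated 25 days, survives | 28 − 2 = 26 | 28 − 2 − 25 = 1 | 28 − 25 = 3 |
| Intubated from simple oxygen on day 2, ventilated to day 28 (27 days), survives | 28 | 28 − 27 = 1 | 1 |
| High-flow 2 days, ventilated 10 days, dead for the last 14 days | 28 − 14 − 2 = 12 | 12 − 10 = 2 | 28 − 14 − 10 = 4 |

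The third row outranks the second under the current wording (26 against 21). The fourth row ties with a patient who never needed support. The last row shows that deaths do lower the score; the fault concerns ventilated days before death or in survivors.

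**Step 2: arm level.** Assumptions, none taken from the documents except the first pair of rates:

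- intubation 25% in control and 15% with prone positioning. These are the section 13.1 rates for intubation or death, borrowed here as intubation rates;
- the 10 per 100 who are spared recover after h = 5 to 10 days of high-flow;
- intubated patients have b = 0 to 4 days of high-flow first and v = 10 to 20 ventilated days;
- no deaths, and all other patients alike in both arms.

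Only the shifted 10% contributes to the difference, prone minus control:

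- As written: 0.10·[(28 − h) − (28 − b)] = 0.10·(b − h). Range: 0.10·(0 − 10) = −1.0 to 0.10·(4 − 5) = −0.1 days.
- After the change: 0.10·(b + v − h). Range: 0.10·(0 + 10 − 10) = 0.0 to 0.10·(4 + 20 − 5) = +1.9 days.

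**Step 3: a more favourable course.** Suppose instead that the spared patients never need high-flow. The difference as written is 0.10·b, that is 0.0 to +0.4 days. After the change it is 0.10·(b + v), that is 0.10·(0 + 10) = +1.0 to 0.10·(4 + 20) = +2.4 days. The sign is no longer wrong, but averted ventilator days still earn nothing.

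**The case against.** **It measures a narrow objective, and intubation is captured elsewhere.** Section 3.2 asks about use of NIV or high-flow, and intubation is in both the primary composite and the ventilation-free-days endpoint. This limits the damage, since a reader with all the results can see the intubations. It does not repair this endpoint, which is reported with its own probabilities. An endpoint that already counts death as failure is also more than a tally of device use.

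**It can be left to the SAP.** A missing derivation rule could be. Here the Protocol states the definition in three places, and following it faithfully gives the inverted ranking. Section 13 itself treats altered criteria as a change needing a specific analysis plan.

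**The direction is not established.** This stands. Section 2.2 hypothesises that positioning prevents deterioration from the 3 L/min stage. If it also reduces high-flow use, the endpoint need not point to harm, as step 3 shows. A reader might infer that it must show harm whenever the primary endpoint shows benefit; the documents do not support that.

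**The score of 28 for an intubated patient is extreme.** Also fair: it skips the high-flow step and needs long survival on a ventilator. The inversion does not depend on it, since 26 against 21 arises after passing through high-flow.

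**Conclusion.** The point holds for this one endpoint. As defined, ventilated days of living patients are success days, and the score can place a long-ventilated survivor above a patient who recovered on high-flow. That follows from the wording alone. The arm-level figures (-0.1 to -1.0 days as written, 0.0 to +1.9 after the change) are illustrations resting on the assumptions in step 2.

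Two stronger readings are tempting but not supported.

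- *That about 20% of controls are mis-scored.* The 20% in section 2.3 includes deaths, and days after death are already removed. It also covers patients already on high-flow, whom this endpoint excludes. The number affected cannot be derived from the documents.
- *That maximum oxygen flow also scores intubated patients as doing well.* The peak reached before escalation is kept, so a patient who worsened on standard oxygen keeps a poor value. The endpoint line, "Maximum Flow Rate of Oxygen Therapy Over 28 Days", names no interface; the restriction appears in the objective ("the maximum flow rate of oxygen therapy (nasal or mask") and in data collection ("Maximum Oxygen Therapy Flow Rate (Nasal or Mask"). If high-flow counted as nasal oxygen, escalation would raise the maximum, to as much as 60 L/min on the section 2.1.2 figure. No fixed direction of bias follows.

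The primary endpoint, the maximum of 500 and the stopping rules are untouched. This should be corrected, but it does not threaten the trial's main conclusion.

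**What to change.** Redefine the endpoint in the synopsis, section 4.2 and section 9.1 as *days alive without NIV, high-flow oxygen or invasive ventilation to day 28*, keeping the restriction to patients on neither NIV nor high-flow at baseline.

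No new data are needed: section 6.1.2 already collects vital status, intubation and NIV or high-flow use daily. The cost is the wording in three places and the derivation code.

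The downside is that the endpoint will overlap more with ventilation-free days and will no longer isolate NIV or high-flow use. That use can still be described separately by arm, which serves the section 3.2 objective. Replacing maximum flow with an ordinal support scale would be a design preference and is not needed for this correction.
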